## Research participants data collected daily

Study participants will receive daily (until the tenth day) a secure link via email and / or phone messaging application to complete a questionnaire containing questions on clinical symptoms and use of study medication, and clinical signs (peripheral oxygen saturation and heart rate) that will be measured using a portable oximeter that will be provided to the patient free of charge by the coordinating center. This questionnaire will be stored in the same secure environment as the eCRF.

Follow-up calls will be made by the participating center team on the days 14 and 28. On the day 14 there will be data collection regarding the ordinal clinical scale of symptoms and on the day 28 the follow-up data: hospital admission, survival and use of mechanical ventilation.

## 4. OUTCOMES

### 4.1 Primary Outcome

Decay rate of the SARS-CoV-2 viral load logarithmic curve obtained via nasopharyngeal swab between the baseline and the fifth and tenth days after randomization.

## 4.2 Secondary Outcomes

- I. Hospital admission between randomization and the day 28;
- II. Need for invasive mechanical ventilation between randomization and day 28;
- III. Time to resolve symptoms until the tenth day;
- IV. Ordinal clinical scale of symptoms on day 14 (1. not hospitalized, without limitation of daily activities; 2. not hospitalized, with limitation of daily activities; 3. hospitalized, without the need for supplemental oxygen; 4. hospitalized, requiring supplemental oxygen; 5 hospitalized, requiring high-flow nasal oxygen therapy, non-invasive mechanical ventilation, or both; 6. hospitalized, requiring blood oxygenation through a membrane system, invasive mechanical ventilation, or both; 7. Death).

## 4.3 Secondary Safety Outcomes

- I. Grade 1, 2, 3 and 4 adverse events, which were not present at the patient's entrance, defined by the *Division of AIDS (DAIDS) Table for Grading the Severity of Adult and Pediatric Adverse Events* (corrected version 2.1, July, 2017).
- II. Bleeding, as defined in table 5:
  - a. Major bleeding
  - b. Clinically relevant non-major bleeding,
  - c. Minor bleeding;
- III. Adverse events (AE) and serious adverse events (SAE);
- IV. Discontinuation of study drug-related treatment.

**Table 5.** Bleeding classification

| Type  | Definition                                                                                                                                                                                                                                                                                                                                                      |
|-------|-----------------------------------------------------------------------------------------------------------------------------------------------------------------------------------------------------------------------------------------------------------------------------------------------------------------------------------------------------------------|
| Major | Defined as clinical bleeding associated with any of the following: fatal outcome, critical site involvement (intracranial, intraspinal, intraocular, pericardial, intra-articular, intramuscular with compartmental or retroperitoneal syndrome), or clinical bleeding with a drop in hemoglobin concentration $\geq 2\text{g/dL}$ , or need for transfusion of |

|                                      |                                                                                                                                                                                                                                                                 |
|--------------------------------------|-----------------------------------------------------------------------------------------------------------------------------------------------------------------------------------------------------------------------------------------------------------------|
|                                      | ≥2 units of packed red blood cells or whole blood. All intracerebral (or intraparenchymal) bleeds are included in the primary analysis as hemorrhagic stroke.                                                                                                   |
| Clinically relevant non-major | Defined as clinical bleeding that does not present major bleeding criteria, but requires medical intervention, unscheduled contact (in person or by telephone) with a doctor, temporary interruption of the study drug, pain or impairment of daily activities. |
| Minor                         | Defined as clinical bleeding that does not meet criteria for clinically relevant major or non-major bleeding.                                                                                                                                                   |

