| Safety outcomes       | 
 
1. Grade 1, 2, 3 or 4 adverse events, which were not presented when the patient entered the study. Defined by the AIDS division (DAIDS) Table for grading the severity of adult and
 
                                                                                                                                                                                                                                                                                                                                                                                                                                                                                                                                                  |

|                                               |                                                                                                                                                                                                                                                                                                                                                                                                                                                                                                                                                                                                                                                                                                                                                                                                                                                                                                   |

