There are potential risks related to the use of halofuginone. The main risks are gastrointestinal symptoms such as nausea and vomiting, as well as fatigue. Regarding nausea and vomiting, antiemetics will be prescribed and provided free of charge to patients, following the guidelines of the protocol. Another potential risk of the use of halofuginone refers to a greater chance of bleeding, however, this risk is mitigated by clear and specific criteria and exclusion, not allowing the inclusion of patients with a high risk of bleeding in the study.

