## 8.6 Reporting adverse events

### 8.6.1 *Adverse Events (AE)*

An adverse event (AE) is any unfavorable medical occurrence in a clinical study participant who has been administered a drug and who does not necessarily have a causal relationship to treatment. An AE can, therefore, be any unfavorable and/or unintended sign, symptom or disease, temporarily associated with the use of a study drug, and whether or not considered to it. AEs may also include pre- or post-treatment complications that occur as a result of procedures specified in the protocol, lack of efficacy, overdose, reports of drug abuse/misuse or professional exposure. Pre-existing events that increase in severity or change in nature during or as a result of participating in the clinical study will also be considered AEs.

An AE does not include the following:

- Medical or surgical procedures, such as surgery, endoscopy, tooth extraction and transfusion. The condition that led to the procedure can be an adverse event and must be reported.
- Pre-existing diseases, conditions or laboratory abnormalities present or detected before entering the study that do not get worse
- Situations in which an undesirable medical event has not occurred (for example, hospitalization for elective surgery, social and/or convenience admissions)
- Overdose without clinical sequelae
- Any medical condition or clinically significant laboratory abnormality with a start date prior to the date of signing the consent form, and not related to a procedure associated with the protocol. It is considered pre-existing and must be documented in the medical history and CRF

All adverse events must be recorded by the investigators on the clinical records (CRF), regardless of severity.

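### The DAIDS-graded adverse-event outcome counts only events absent at entry, while section 8.6.1 counts worsening of pre-existing events, so worsened nausea or vomiting drops out of the graded comparison between arms

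*Protocol*

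**What the plan says.** Protocol section 4.3, item I, defines the graded safety outcome as "Grade 1, 2, 3 and 4 adverse events, which were not present at the patient's entrance", graded on the DAIDS table. The synopsis has the same restriction: "Grade 1, 2, 3 or 4 adverse events, which were not presented when the patient entered the study". Neither place has a clause for worsening.

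Section 8.6.1 takes a different line. Its definition of an adverse event extends to "Pre-existing events that increase in severity or change in nature during or as a result of participating in the clinical study". Its list of exclusions removes prior illnesses and laboratory findings "present or detected before entering the study that do not get worse", which implies that those that do get worse remain in. All adverse events are to be recorded, whatever their severity.

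Section 4.3 lists three further safety outcomes: bleeding in three tiers (item II), adverse and serious adverse events without grade or entry restriction (item III), and drug-related discontinuation (item IV). The synopsis version of item III names only serious adverse events.

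On the population and the drug: section 3.4.1 requires mild or moderate symptoms at inclusion; the symptom list for the Day 14 call in section 3.8.4 includes nausea and vomiting; and section 8.4 says of halofuginone that "The main risks are gastrointestinal symptoms such as nausea and vomiting, as well as fatigue".

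**The concern.** The protocol gives two incompatible answers to one question: does a symptom already present at entry count when it worsens on treatment? Section 8.6.1 says yes; outcome I, taken at its word, says no.

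The conflict matters here because the expected toxicity overlaps with the disease. Every patient enters with symptomatic COVID-19, nausea and vomiting are among the symptoms that the protocol tracks, and they are also the leading expected drug effects. Section 3.10.4 describes the gastrointestinal effects as dependent on dose. With two active doses and placebo, a change in grade is one of the more informative safety signals available, and outcome I is where grade is compared. A patient who enters with Grade 1 nausea and reaches Grade 3 on study drug would contribute nothing to it.

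This is not a detail left to the statistical analysis plan. The protocol fixes the outcome definition itself, in two places. An analysis plan that followed section 4.3 would carry the exclusion forward, and one that followed section 8.6.1 would depart from the stated outcome.

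**Working it through.** **Step 1. The passages side by side.** The protocol states no figure on this point, so there is none to reproduce. Take a patient with nausea at entry and follow three courses under each definition:

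| Course on study drug | AE under 8.6.1 | Outcome I (graded), read literally | Outcome III of 4.3 (ungraded) |
|---|---|---|---|
| No nausea at entry, Grade 2 later | yes | counted | counted |
| Grade 1 at entry, stays Grade 1 | no | not counted | not counted |
| Grade 1 at entry, reaches Grade 3 | yes | **not counted** | counted, without grade |

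The definitions part only in the third row. The event is recorded, but its grade does not enter the graded comparison.

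**Step 2. What this does to a comparison of risks.** This is an illustration. The 50 patients per arm come from protocol section 5; every rate below is assumed. Let the true risk of new or worsened nausea be 40% in one active arm and 15% on placebo, and let a share *b* of patients in each arm have nausea at entry. Randomisation makes *b* similar across arms in expectation. Assume also that the risk is the same in patients with and without nausea at entry.

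- Patients per arm who can score = 50 × (1 − b)
- Recorded risk with all 50 as denominator = true risk × (1 − b)
- Recorded risk difference = (0.40 − 0.15) × (1 − b)
- Recorded risk ratio = [0.40 × (1 − b)] / [0.15 × (1 − b)] = 0.40 / 0.15 = 2.67, whatever *b* is

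Power is the usual normal approximation for two proportions, two-sided 5%: Φ[(d − 1.96 × se₀) / se₁], with se₀ from the pooled and se₁ from the separate variances. At b = 0 the pooled risk is 0.275, so se₀ = √(0.275 × 0.725 × 2/50) = 0.0893 and se₁ = √(0.40 × 0.60/50 + 0.15 × 0.85/50) = 0.0857. Then (0.25 − 1.96 × 0.0893)/0.0857 = 0.87, and Φ(0.87) is about 0.81.

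| b (assumed) | Can score, per arm | Recorded risks, all 50 | Difference | Power, all 50 as denominator | Power, only those free of nausea at entry |
|---|---|---|---|---|---|
| 0 | 50 | 40.0% v 15.0% | 25.0 points | 80.9% | 80.9% |
| 10% | 45 | 36.0% v 13.5% | 22.5 points | 74.9% | 76.6% |
| 20% | 40 | 32.0% v 12.0% | 20.0 points | 68.0% | 71.5% |
| 30% | 35 | 28.0% v 10.5% | 17.5 points | 60.5% | 65.5% |
| 40% | 30 | 24.0% v 9.0% | 15.0 points | 52.5% | 58.6% |

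**Step 3. Reading the table.** With all randomised patients in the denominator, the absolute difference shrinks in proportion to the share symptomatic at entry, and the ratio is unchanged. With only patients free of the symptom at entry in the denominator, this model gives no bias, only fewer patients. Information is lost in both cases.

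**Step 4. Can a change in grade be derived from what is collected?** Section 3.11.5 lists clinical symptoms among the Day 1 data and questions on symptoms in the daily questionnaire to Day 10. It does not say that severity or a DAIDS grade is recorded at either point.

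**The case against.** **The two sections can be read together.** Outcome I uses the term adverse events, which 8.6.1 defines to include worsening, and one may argue that Grade 3 nausea was not present in a patient who entered with Grade 1. The English is loose elsewhere too. This reading is possible, but section 4.3 and the synopsis do not state it, and a definition that needs it should be reworded. The last exclusion in 8.6.1, for conditions that began before consent, also lacks a worsening clause. It only labels them pre-existing, however, and the main definition says what happens when such events worsen.

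**Worsened events are not lost.** This stands. A reader might infer that the trial will not see them, but 8.6.1 requires that they be recorded, item III of section 4.3 covers them, and section 6.2 has the data monitoring committee consider the number of adverse events by arm. The defect is confined to the graded comparison. The cover does rest on section 4.3 and 8.6.1, since the synopsis version of item III names only serious events.

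**No general bias follows.** This also stands. A reader might conclude that toxicity and dose comparisons are biased towards no difference. Under the model above that holds for the absolute difference with all patients as denominator, not for the risk ratio, and the protocol fixes neither the denominator nor the effect measure. No safety outcome enters the sample size calculation in section 5.

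**Two further limits.** Outcome I is not the only safety outcome with severity levels, since bleeding is tiered; it is the only one on the DAIDS scale. It is tempting to add fatigue to the overlapping symptoms, but it is missing from the list in section 3.8.4, so its presence at entry is inference. That list is itself for Day 14 and gives no prevalence at entry.

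**Conclusion.** The point holds in a limited form. Section 4.3 item I and the synopsis contradict section 8.6.1 on whether worsening of a pre-existing event counts. Taken literally, they remove worsened nausea and vomiting from the only DAIDS-graded comparison, in a population that enters symptomatic and for effects that the protocol names as main risks of the drug.

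The consequence is lost information and, with all randomised patients as denominator, a smaller absolute difference. How much smaller is unknown: the 10% to 40% at entry, the risks of 40% and 15%, and the equal risk in patients with and without the symptom at entry are all assumptions. The documents do not support the stronger conclusions that such events go unrecorded or that the risk ratio is biased. The definition should be corrected, but this is a secondary safety outcome and the primary analysis is not affected.

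**What to change.** In section 4.3 item I and in the synopsis, define outcome I as DAIDS Grade 1 to 4 events that are new, or that increase in grade from baseline, consistent with section 8.6.1.

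The cost in text is one sentence in each place. Before adopting it, check the Day 1 form and the daily questionnaire. If both already capture severity, nothing else changes. If they record only the presence of symptoms, a severity field is needed in both so that the change in grade can be derived; this means revising the electronic form and the patient questionnaire.

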## 5. SAMPLE SIZE

Based on data from the Wölfel et al. study (2020), an average linear decay rate for patients with SARS-CoV-2 in nasopharyngeal swab assessed from the fourth to the fourteenth day of symptom onset is  $1.7 \log_{10}$  every 5 days. Assuming this decay rate for the placebo group, considering the scenario that all selected active treatments will have a decay rate of  $2.2 \log_{10}$  (viral load), 150 patients with SARS-CoV-2 confirmed by RT-PCR (50 per group) will have 90% power to indicate that at least one of the treatments will be superior to the placebo, considering a two-tailed significance level of 2.7%, to guarantee an overall level of significance of 5%. The sample calculation was performed using simulations considering different standard deviations in each time step (baseline, 5 days and 10 days), and an auto-regressive correlation of 0.85. The covariance matrix was based on unpublished data on the daily viral load of [name] [name] (Fiocruz).

## **6.2 Safety interim analysis**

A safety interim analysis is planned after 60 patients have reached the outcome of the 28-day follow-up study. The Data Monitoring Committee (DMC) will use the Haybittle-Peto rule, considering  $p < 0.001$ , to interrupt the study for safety reasons. In view of the outcome of the study and sample size, the interim analysis will not include an analysis of effectiveness. In this analysis, the DMC will also consider safety issues such as the number of adverse events between the arms to make a decision. The Haybittle-Peto rule will be used as a reference, not as a strict rule. DMC will also consider the effect on other secondary outcomes, in particular on adverse events, and on new external evidence available during the conduct of the clinical study. We will not adjust the final hypothesis test values for sequential analysis

## **7. DATA QUALITY CONTROL**

### **7.1 Data quality assurance**

The quality and inconsistencies of the data will be periodically assessed by the IP-HCor data management team. Inconsistencies will be reported to the centers for possible reassessments and corrections. Once it is identified that a center has shown a high frequency of inconsistencies, monitoring will be carried out to verify the information in the source documents and new training of the team to collect and insert the data into the system.

Several procedures are planned to guarantee the quality and traceability of the data inserted in the system, including, but not limited to:

- All researchers will participate in a training session before the start of the study to ensure consistency of the study procedures, including data collection;
- Investigators will be able to call the Coordinating Center study to resolve issues or problems that may arise;
- Data cleaning to identify inconsistencies will be conducted periodically (every fifteen days). The centers will be notified of inconsistencies in order to provide correction;
- The IP-HCor data management team will review detailed reports on screening, inclusion, follow-up, consistencies and completeness of the data on a monthly basis.
- Immediate actions will be taken to resolve any problems.

Monitoring in the participating centers will be carried out during the conduct of the study in particular if there are special needs due to the accumulation of inconsistencies or missing data.

## **8. ETHICAL ASPECTS AND GOOD CLINICAL PRACTICE**

The study will be conducted in accordance with current national regulations, described in the following documents:

- Resolução CNS/MS No. 466, of December 12, 2012 and its complementaries from CNS/MS;
- Resolução CNS/MS No. 441, of May 12, 2011 and Portaria No. 2.201, of September 14, 2011.
- Document of the Americas.

### **8.1 Study Approval**

The ethical approval will be obtained according to all applicable regulatory obligations. All the ethical and regulatory approvals must be available before any

procedure involving the research subject, including the screening tests to verify ones eligibility,

Considering the provisions of the CONEP guidance letter “Guidelines for conducting CEP research and activities during the pandemic caused by the SARS-COV-2 coronavirus (COVID-19)”, dated May 9, 2020, item 2.1.2, where it says: “In the case of research protocols that have “participating centers” and / or “co-participating centers”, no new ethical analysis should be carried out by the respective linked CEPs. Due to the exceptional character adopted, CEPs will endorse the approved opinion, when applicable, issued by CONEP”. The participating centers must wait for a referenced opinion from their institution's CEP to start the study at the institution.

In addition, protocol amendments should be implemented only after due approval by the CEP/CONEP System, following the orientations described above, except in situations where the implementation of the amendment prior to the approval of the CEP/CONEP system aims to protect research participants. In this case, the CEP/CONEP system must be notified of this implementation.

## 8.2 Informed Consent Process

Each research participant or their legal representative must provide their written consent in accordance with local requirements, after the nature of the study has been fully explained. The ICF(s) must be signed before any activity related to the study is carried out. The ICF(s) that are used must be approved by the coordinating center and by the REC of the participating centers, and must be in a language that the research participant is able to read and understand. Informed consent must comply with the principles originated in Resolução 466/12 of the National Health Council and with the guidelines of Good Clinical Practices.

Prior to inclusion in the study, the investigator or an authorized member of the research center team must explain to potential research participants or their legal representative the purposes, methods, reasonably anticipated benefits and potential risks of the study, as well as any discomfort that participation in the study may cause. Research participants or their legal representatives will be informed that their

participation is voluntary and that they will be able to withdraw their consent to participate at any time. They will be informed that the choice not to participate will not affect the care they will receive to treat their illness.

Finally, they will be informed that the investigator will keep a record of identification of the research participants and that their records will be accessible by health authorities and the authorized team of the coordinating center without violation of the research participant's confidentiality, at the level permitted by applicable law(s) or regulation(s).

The research participant or his legal representative will have enough time to read the ICF and will have the opportunity to ask questions. After this explanation and before entering the study, consent must be properly registered through the dated personal signature of the research participant or his legal representative and whoever explained it. After obtaining consent, a copy of the ICF must be provided to the research participant. This entire process must be documented in the participant's source document.

